### Observational cohort for patients who do not want to undergo randomisation

Previous studies have shown that inclusion of older adults with cancer can be challenging.^28^ One reason is that patients or their physicians may strongly prefer a particular treatment strategy and therefore do not want to undergo randomisation. To still capture all eligible patients and assess differences in tumour and patient characteristics between participants and non-participants, we will register patients in an observational study arm. Patients need to provide written consent for the observational cohort but will not be randomised. They will be invited to complete the G8, Katz ADL, Lawton IADL and EQ-5D and questions about living status, previous falls and delirium at baseline and will receive one follow-up request at 3 months for the EQ-5D, Katz ADL, Lawton IADL.

### Data collection, management and monitoring

Clinical data will be extracted from electronic health records and collected on electronic case report forms designed for this study. Castor EDC, an EDC system, is used for data entry and storage. On site monitoring is organised according to the Netherlands Federation of University Medical Centers guideline ‘Quality assurance of research involving human subjects’^29^ by dedicated monitors from the Leiden University Medical Center. As the study compares two frequently used and well-characterised chemotherapy regimens conform clinical practice, the study is classified as low risk and does not require a Data and Safety Monitoring Board or interim analysis.

#### Ethics and dissemination

This trial has received ethical approval by the ethical committee Leiden Den Haag Delft (P24.018) and will be approved by the Institutional Ethical Committee of the participating institutions. All participants will provide written informed consent and the study will adhere to the principles outlined in the Declaration of Helsinki. The results will be disseminated in peer-reviewed scientific journals.

#### Statistics: sample size and power calculations

Based on previous studies in older adults with metastatic colorectal cancer (table 2), the study assumes non-inferiority of the intervention arm with a median PFS of 8 months. We determined a non-inferiority margin of 8 weeks based on previous trials^16 17^ and extensive consultation with seven primary investigators from participating hospitals and the Dutch colorectal patient foundation, who all considered this an acceptable upper margin for non-inferiority.

**Table 2 T2:** Median PFS in previous trials with older adults

Trial	Patient population	Median PFS
MRFOCUS2^15^	‘Non-fit’ older or frail mCRC patients receiving upfront dose reduction	Median PFS was 3.5, 5.8, 5.2 and 5.8 months in the 5-FU monotherapy, FOLFOX, capecitabine monotherapy and CAPOX groups, respectively; a reasonable estimate for all patients is 5 months
AVEX^33^	Older mCRC patients, no candidate for oxaliplatin or irinotecan	Median PFS 9.1 months for capecitabine+bevacizumab, 5.1 months for capecitabine monotherapy.
NORDIC9^16^	‘Non-fit’ older mCRC patients	Median PFS 5.1 months for full-dose S-1, 6.2 months for reduced-dose oxaliplatin+S-1. 25% received bevacizumab.
SALTO^34^	mCRC patients with median age 73 years (not specifically older patients)	Median PFS 8.2 months for capecitabine monotherapy, 8.4 months for S-1 monotherapy.

AVEXAVastin in the Elderly with XelodaCAPOXcapecitabine plus oxaliplatinFOLFOXfolinic acid, fluorouracil, and oxaliplatin5-FUFluorouracilmCRC, metastatic colorectal cancerPFSprogression-free survival

A non-inferiority logrank test with an overall sample size of 528 subjects (264 in the reference group and 264 in the treatment group) achieves 80.0% power at a 5% significance level to detect an equivalence HR of 1.25 when the actual HR is an equivalence HR of 1 and the reference group hazard rate is 0.12. The study will last for 48 time periods of which subject accrual entry occurs in the first 36 time periods. The accrual pattern across time periods is uniform (all periods equal). Accounting for an expected dropout rate of 10%, 587 patients in total are required.

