**Methods and analysis:**

The DOSAGE study is an investigator-initiated phase III, open-label, non-inferiority, randomised controlled trial in patients aged≥70 years with metastatic colorectal cancer eligible for palliative chemotherapy. Based on toxicity risk, assessed using the Geriatric 8 (G8) tool, patients will be stratified to either doublet chemotherapy (fluoropyrimidine with oxaliplatin) or fluoropyrimidine monotherapy. Patients classified as low risk will be randomised between a fluoropyrimidine plus oxaliplatin in either full-dose or with an upfront dose reduction of 25%. Patients classified as high risk will be randomised between fluoropyrimidine monotherapy in either full-dose or with an upfront dose reduction. In the dose-reduced arm, dose escalation after two cycles is allowed. The primary outcome is PFS. Secondary endpoints include grade≥3 toxicity, QoL, physical functioning, number of treatment cycles, dose reductions, hospital admissions, overall survival, cumulative received dosage and cost-effectiveness. Considering a median PFS of 8 months and non-inferiority margin of 8 weeks, we shall include 587 patients. The study will be enrolled in 36 Dutch Hospitals, with enrolment scheduled to start in July 2024. This study will provide new evidence regarding the effect of dose-reduced chemotherapy on survival and treatment outcomes, as well as the use of the G8 to choose between doublet chemotherapy or monotherapy. Results will contribute to a more individualised approach in older patients with metastatic colorectal cancer, potentially leading to improved QoL while maintaining survival benefits.

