### Statistics: analysis

Both per-protocol and an intention-to-treat analysis will be conducted. Patients will be grouped according to the treatment they were randomised to receive. Descriptive characteristics of patients will be reported using frequencies and proportions for categorical data and means and SD for continuous data.

*Primary outcome* PFS will be estimated from randomisation by using Kaplan-Meier’s methodology and Cox regression models. Non-inferiority of the dose-reduced arm can be claimed if the upper limit of the CI of the HR is below 1.25. Univariable and multivariable Cox proportional hazard regression models will be estimated to investigate the effect of age, comorbidity, the geriatric domains, cumulative received dose and tumour characteristics on survival. To study the effect of treatment among risk groups, an interaction term between will be included in the model together with additional targeted therapy and centre. As an exploratory planned subgroup analysis, PFS will be stratified based on molecular pathologic features.

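### At the stated 8-month median, the announced 8-week margin is HR 1.30, but the sample size and decision rule use HR 1.25 (about 7 weeks)

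*Protocol article*

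**What the plan says.** The abstract (Methods and analysis) derives the trial size from a margin in weeks: "Considering a median PFS of 8 months and non-inferiority margin of 8 weeks, we shall include 587 patients".

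The section on sample size and power repeats that margin: "We determined a non-inferiority margin of 8 weeks based on previous trials". It adds that seven primary investigators and the Dutch colorectal patient foundation were consulted and found it acceptable as an upper limit. On the median it says "the study assumes non-inferiority of the intervention arm with a median PFS of 8 months".

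The calculation in the same section is on the hazard ratio scale. The test is "to detect an equivalence HR of 1.25 when the actual HR is an equivalence HR of 1", with the condition that "the reference group hazard rate is 0.12", and it "achieves 80.0% power at a 5% significance level". The result is 528 patients, or 587 after 10% dropout.

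The analysis section gives one decision rule: "Non-inferiority of the dose-reduced arm can be claimed if the upper limit of the CI of the HR is below 1.25". The article does not show how 8 weeks became 1.25.

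**The concern.** A margin in weeks and a margin as a hazard ratio are the same margin only at one particular reference median. The article gives 8 weeks, 8 months and HR 1.25 as if they belonged together, and they do not.

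The margin is the threshold for the trial's main conclusion, and its clinical justification is the agreement of the people consulted. They were asked about 8 weeks. A reader who sees non-inferiority declared will take it that a loss of 8 weeks was the limit, when the limit applied was a different quantity. A result with an upper confidence limit of 1.28 shows the difference. It fails the written rule, yet at an 8-month reference median it is 8 − 8/1.28 = 1.75 months, or 7.6 weeks, which is inside the announced margin.

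**Working it through.** **Inputs.** Margin of 8 weeks and median of 8 months (abstract; sample size section). HR margin 1.25, true HR 1, hazard 0.12, 80% power, 5% significance, 528 patients allocated 1:1, 36 accrual periods out of 48, 10% dropout (sample size section). Threshold 1.25 (analysis section). Assumptions: exponential PFS, in line with the constant hazard in the plan; periods are months; 30.4375 days (4.348 weeks) per month, so 8 weeks = 56/30.4375 = 1.84 months.

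**1. The plan's own figure.**
- Events = 4(z_α + z_β)²/(ln HR)². With one-sided 5% and 80% power, 4(1.645 + 0.842)²/(ln 1.25)² = 497.
- Event probability with uniform accrual = 1 − (e^(−12h) − e^(−48h))/(36h). At h = 0.12 this is 0.946.
- N = 497/0.946, about 526 (530 with Freedman's formula), against 528 stated. Power at 528 is 80.2%. 528/0.9 = 587.
- Two-sided 5% does not reproduce it: 631 events, N = 668.

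So 528 and 587 follow from HR 1.25, hazard 0.12 and one-sided 5%. Neither 8 weeks nor 8 months enters.

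**2. Converting the margin.** HR = median/(median − loss), and loss = median × (1 − 1/HR).

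| Reference median | HR 1.25 as a loss | 8 weeks as an HR |
|---|---|---|
| 8 months (stated) | 8 − 6.4 = 1.6 months = 7.0 weeks | 8/(8 − 1.84) = 1.30 |
| 5.78 months (ln 2/0.12) | 1.16 months = 5.0 weeks | 5.78/(5.78 − 1.84) = 1.47 |

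The two margins coincide when 0.2 × median = 1.84 months, that is, at a median of 9.2 months. Below it HR 1.25 is stricter than 8 weeks; above it HR 1.25 is looser.

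**3. What 8 weeks at 8 months would have required.** With HR 1.299, one-sided 5% and 80% power, 363 events are needed. At hazard ln 2/8 = 0.0866 the event probability is 0.892, so N = 408, or 454 with dropout. At hazard 0.12, N = 384, or 427 with dropout. A two-sided 5% level at 0.0866 gives 460 events and N = 516, or 574 with dropout. That is near 587 but not equal to it, and it uses neither the HR nor the hazard that the article states.

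**4. HR 1.25 if the median really is 8 months.** 528 × 0.892 = 471 events expected, and power at one-sided 5% is 78.1%. For 80%, N would be 497/0.892, about 558, or 620 with dropout.

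**The case against.** The strongest reply is that nothing operative is in doubt. HR 1.25 is both the margin in the calculation and the only criterion in the analysis, and the sample size reproduces. That stands. A reader might infer that two competing tests exist or that the decision rule is ambiguous. The article does not support this, because it sets no test in weeks.

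Second, the direction is safe. The consulted parties accepted 8 weeks as an upper limit, and at 8 months HR 1.25 is tighter. This also stands at any reference median below about 9.2 months. A reader might infer a raised risk of falsely claiming non-inferiority against the announced margin, but at the planned median there is none. Above 9.2 months the order reverses, though only slightly at first: at 10 months HR 1.25 is 2.0 months, or 8.7 weeks.

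Third, a median close to 9.2 months does occur. Table 2 lists 9.1 months for capecitabine plus bevacizumab, where HR 1.25 is 1.82 months, or 7.9 weeks, and the protocol permits bevacizumab. However, the article does not adopt that value as its planning median.

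Fourth, the article attaches the 8 months to the intervention arm. With 8 weeks rounded to 2 months, 10/8 is exactly 1.25 (9.84/8 = 1.23 without rounding). This may be where the number came from. It does not rescue the text, because it needs a 10-month reference median (hazard 0.069). No such median is stated, and it conflicts with a true HR of 1 and a hazard of 0.12.

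**Conclusion.** The point holds as a mismatch between the announced margin and the tested one. At the stated 8-month median, 8 weeks is HR 1.30 and the test uses HR 1.25, which is 7.0 weeks. The difference is about one week, or 0.05 on the hazard ratio scale, on the strict side. The abstract's statement that 8 months and 8 weeks lead to 587 is not correct as written. The stakeholder agreement was given for a quantity other than the one tested.

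A reader might take the wider figures (5.0 weeks, HR 1.47) as the size of this mismatch. They arise from a separate conflict, between the hazard of 0.12 and the 8-month median, and should not be charged to the margin. Nor is the sample size arithmetic wrong: it is right for its stated inputs.

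The conclusion rests on exponential PFS with proportional hazards. The 5.8-month median and the power figures also take periods as months, and the power figures a one-sided 5% level. The article states neither the unit of the periods nor the sidedness.

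**What to change.** Keep HR 1.25 as the single non-inferiority criterion. In the abstract and the sample size section, replace 8 weeks as the margin with HR 1.25 and its absolute equivalent at one stated reference median: about 7 weeks at 8 months (8.0 against 6.4 months), or about 5 weeks at the 5.8 months implied by hazard 0.12 per month. Add that this lies within the 8 weeks that the consulted parties accepted, so their agreement still covers it.

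Reconcile the hazard with the median in the same edit. Otherwise the restated margin would be anchored to a median that the sample size does not use. If 8 months stands, replace 0.12 with 0.0866 and restate power at 528 as about 78% (one-sided 5%, periods as months). If 0.12 per month stands, give the median as 5.8 months; the 80% power is then unaffected.

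The cost is wording, plus a slightly less favourable stated margin and, if 8 months is kept, slightly lower stated power. Enrolment does not change. The edit should be made before any outcome data are seen, since a margin clarified afterwards would look data-driven.

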#### Trial status

Expected date of first inclusion is July 2024 and the study is expected to end in January 2029.

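### The sample size uses a hazard of 0.12 per period (median PFS about 5.8 months), not the stated 8-month median; at 8 months, 528 patients give about 78% power rather than 80.0%

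*Protocol article*

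**What the plan says.** In the protocol article, under the sample size and power heading, "the study assumes non-inferiority of the intervention arm with a median PFS of 8 months". The abstract gives the same basis for the enrolment target: "Considering a median PFS of 8 months and non-inferiority margin of 8 weeks, we shall include 587 patients".

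The calculation in that statistics section is for a non-inferiority log-rank test with 528 patients, 264 per arm. It "achieves 80.0% power at a 5% significance level" and is designed "to detect an equivalence HR of 1.25 when the actual HR is an equivalence HR of 1". Its event rate enters through one number: "the reference group hazard rate is 0.12". On timing, "The study will last for 48 time periods of which subject accrual entry occurs in the first 36 time periods", with uniform accrual. A 10% dropout allowance takes 528 to 587.

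The article states no required number of events. It does not say how long a time period is or whether the 5% is one-sided. Under Trial status it adds: "Expected date of first inclusion is July 2024 and the study is expected to end in January 2029".

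**The concern.** Under the constant hazard that such a calculation assumes, hazard and median determine each other: hazard = ln 2 / median. A median of 8 months and a monthly hazard of 0.12 cannot both hold.

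The difference matters because the hazard sets the share of patients with a PFS event by the analysis, and the number of events sets the power. A hazard that is too high makes events appear to arrive faster than they will, so fewer patients seem to be needed. If 8 months is the real expectation, the stated power is too high for the stated design. If 0.12 is the real expectation, the median given in both the abstract and the statistics section is wrong, and so is a reader's sense of how much PFS an HR of 1.25 gives away.

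**Working it through.** **Inputs from the article.** Margin HR 1.25; true HR 1; power 80.0%; significance level 5%; 1:1 allocation; hazard 0.12; uniform accrual over 36 periods; 48 periods in total; 528 patients before dropout; 10% dropout; stated median 8 months.

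**Assumptions.** A period is one month, PFS is exponential, and the 5% is one-sided. The last is checked in step 2.

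**1. Hazard against median.**
- ln 2 / 0.12 = 5.78 months. If 0.12 is rounded from anywhere between 0.115 and 0.125, the median lies between 6.0 and 5.5 months.
- ln 2 / 8 = 0.0866 per month.
- Could a period be longer than a month? For 0.12 to mean 8 months, a period would have to be 8 / 5.78 = 1.38 months. The 48 periods would then last about 66 months, but July 2024 to January 2029 is 54 months. The monthly reading is the one that fits.
- The 8 months is worded for the intervention arm, but with a true HR of 1 the reference arm has the same median.

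**2. Reproducing the plan's figure.**
- Events needed (Schoenfeld): d = 4(1.645 + 0.842)² / (ln 1.25)² = 496.7, so 497.
- Event probability: p = 1 − [exp(−12λ) − exp(−48λ)] / (36λ).
- At λ = 0.12, p = 0.946 and N = 496.7 / 0.946 = 525, close to 528.
- At a 6-month median (λ = 0.1155, which rounds to 0.12), p = 0.941 and N = 527.9, so 528.
- Two-sided 5% would need 631 events and about 667 patients, which does not reproduce 528.
- Dropout: 528 / 0.9 = 586.7, so 587.

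The stated sample size is therefore consistent with 0.12 and one-sided 5%.

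**3. The same design at a median of 8 months.** Power = Φ(√(d/4) × ln 1.25 − 1.645).

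| Setting | p | Events from 528 | Power |
|---|---|---|---|
| λ = 0.12, 48 months | 0.946 | 499 | 80.2% |
| λ = 0.0866, 48 months | 0.892 | 471 | 78.1% |
| λ = 0.0866, 54 months | 0.936 | 494 | 79.8% |
| λ = 0.0866, 55 months | 0.941 | 497 | 80.0% |

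The shortfall at 48 months is 497 − 471 = 26 events. Restoring 80% in the 36/48 design would take 496.7 / 0.8917 = 557.01, so 558 evaluable patients, and 558 / 0.9 = 620 enrolled.

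**4. What HR 1.25 means in weeks.** With exponential PFS, the median falls from m to m / 1.25, a loss of 0.2m. With 4.35 weeks per month:
- m = 8: 1.6 months, about 7.0 weeks.
- m = 6: 1.2 months, about 5.2 weeks.
- m = 5.78: 1.16 months, about 5.0 weeks.

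**The case against.** The strongest reply is that the effect is too small to matter. Power drops by about 2 points, and only if the data are cut at month 48. Nothing in the article fixes such a cut: the 48 periods are an input to the calculation. If follow-up reaches the expected study end, the shortfall is 3 events. The 471 also counts nothing from the 59 patients added for dropout. If all 587 were followed fully, there would be 587 × 0.892 = 523 events and 81.8% power. If those 59 gave half their expected events, about 26, the target of 497 would be met at month 48. All of this stands, and it limits the size of the point. It does not make the two stated numbers agree.

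A reader might infer four stronger things that the document does not support:

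- **That 0.12 came from treating 8 months as a mean (1/8 = 0.125).** This is conjecture and fits poorly: 0.125 gives N of about 522, whereas a 6-month median gives 528.
- **That 48 planning periods contradict the 54-month calendar.** An expected study end may include extra follow-up, slower accrual or close-out.
- **That the 8-week margin falls with the median.** The article rests that margin on previous trials and on consultation with investigators and the patient foundation. It does not say that it was derived from the median.
- **That the lack of an event trigger is itself a defect.** An article commonly leaves data-cut rules to the full protocol or analysis plan.

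**Conclusion.** The inconsistency is real. The article states a median of 8 months and calculates with a hazard that means about 5.8 months (about 6 if rounded), so 528, 587 and 80.0% do not follow from the stated median. At 8 months the 36/48 design gives about 471 events and 78% power. That is a loss of at most about 2 points, which nearly vanishes with 54 months of follow-up and is smaller still if dropouts contribute events.

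The contradiction itself depends only on a constant hazard and monthly periods. The event and power figures also rest on one-sided 5%, which is inferred. With a two-sided 95% interval, 497 events would give only about 70% power and about 631 would be needed. The 497 is therefore derived and conditional; it is not a target that the article sets.

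This is a planning error on the primary endpoint that should be corrected, but it does not threaten the trial.

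**What to change.** Decide which figure was intended and make the abstract and the statistics section agree with it. State the length of a time period and the sidedness of the 5%.

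- **If 8 months is kept:** replace 0.12 with 0.0866. Then either restate the power as about 78% for a 48-month analysis, or time the primary analysis by events: about 497 PFS events at one-sided 5%, expected around month 55 and so close to the January 2029 end date. No extra patients are needed. The cost is a change of wording and a cut-off date that depends on how fast events accrue.
- **If 0.12 is kept:** restate the median as about 6 months. This is more than a wording change. HR 1.25 then corresponds to a loss of about 5 weeks in median PFS (about 7 weeks at 8 months), against a stated margin of 8 weeks, and the text should say so.

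Any event target should be fixed only after the sidedness is settled.

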### Statistics: analysis

Both per-protocol and an intention-to-treat analysis will be conducted. Patients will be grouped according to the treatment they were randomised to receive. Descriptive characteristics of patients will be reported using frequencies and proportions for categorical data and means and SD for continuous data.

*Primary outcome* PFS will be estimated from randomisation by using Kaplan-Meier’s methodology and Cox regression models. Non-inferiority of the dose-reduced arm can be claimed if the upper limit of the CI of the HR is below 1.25. Univariable and multivariable Cox proportional hazard regression models will be estimated to investigate the effect of age, comorbidity, the geriatric domains, cumulative received dose and tumour characteristics on survival. To study the effect of treatment among risk groups, an interaction term between will be included in the model together with additional targeted therapy and centre. As an exploratory planned subgroup analysis, PFS will be stratified based on molecular pathologic features.

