### Doublet chemotherapy

Patients classified as low risk will be randomised between doublet chemotherapy with a fluoropyrimidine (physicians’ choice fluorouracil (5-FU) or capecitabine) and oxaliplatin in either full-dose, or with an upfront dose reduction. In the full-dose arm, the following dosing schemes are allowed:

CAPOX: capecitabine 1000 mg/m^2^ at day 1–14 (every 3 weeks) and oxaliplatin 130 mg/m^2^ at day 1 (every 3 weeks).FOLFOX6: 5-FU 400 mg/m^2^ intravenous bolus at day 1 followed by 2400 mg/m^2^ in 46 hours (every 2 weeks), leucovorin 400 mg/m^2^ day 1 (every 2 weeks) and oxaliplatin 85 mg/m^2^ day 1 (every 2 weeks).

In the dose-reduced arm, patients receive an upfront 25% reduction (75% of full dose).

Addition of targeted treatment (bevacizumab or epidermal growth factor receptor (GFR) inhibition) is allowed. Patients with a moderate renal impairment (GFR 30–50 mL/min) will receive a 25% reduced starting dose of capecitabine in the full-dose arm and a 40% reduced starting dose in the dose-reduced arm.

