### Treatment monitoring

After each treatment cycle, treatment tolerability (chemotherapy-related toxicity according to the Common Terminology Criteria for Adverse Events (CTCAE) V.5.0^18^) will be assessed. Patients in the upfront dose-reduced arm who have tolerated the first two cycles of their treatment well (no occurrence of grade 2–5 toxicity), can (but do not have to) receive dose-escalation to 100% at the discretion of the treating oncologist and after consultation with the patient. In both arms, toxicity may allow for further dose reductions: if patients experience either grade 3–4 toxicity or unacceptable grade 1–2 toxicity that influences QoL, the oncologist can reduce the dose by 25%. The minimal dose is 50% of full dose: if further (unacceptable) toxicity occurs, the treatment should be discontinued. For neuropathy, in case of grade 2 toxicity, oxaliplatin dose is reduced with 25%. In case of grade 3 neuropathy, oxaliplatin is definitively stopped. After 18 weeks of doublet chemotherapy, maintenance therapy with capecitabine or 5-FU (with or without bevacizumab) can be started at the discretion of the treating oncologist. Chemotherapy treatment will be continued until progression, unacceptable toxicity or a patients’ or clinicians’ decision to stop. If patients develop progression or discontinue first-line treatment due to other reasons (such as toxicity), the study will end and any further treatment lines are allowed by the discretion of the oncologist.

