### Outcome measures

The *primary outcome* of the study is PFS, defined as time from randomisation until either radiological or clinical progression or death due to any cause, whichever occurs first. Timepoints of measurements are presented in table 1. In case of clinical progression as judged by the local principal investigator, local investigators should explain the base of clinical progression. *Secondary endpoints* include QoL (measured by the EQ-5D and EORTC Core QLQ-C30 questionnaires after 1, 3, 6, 9 and 12 months), physical functioning (measured with the Katz ADL, the Lawton IADL and home and informal care after 1, 3, 6, 9 and 12 months), grade≥3 chemotherapy-related toxicity according to the CTCAE during study treatment, dose reductions during study treatment, number of treatment cycles, unplanned hospital admissions within the first year, OS, cumulative received dose and cost-effectiveness in the first year. Predictive geriatric markers of poor outcomes will be identified using the baseline GA.

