#### Secondary outcomes

A logistic regression model will be estimated to study the effect of groups on chemotherapy-related toxicity; the same covariates as discussed before will be included. Due to the presence of repeated measures for QoL and physical functioning, mixed models to investigate the relation between the outcomes and arms will be used. An interaction term between time and arms will be added to the model to quantify the effect of time. The cumulative dose received by patients in each arm (divided by BSA) will be reported, and means will be compared using the t-test. Finally, we will investigate which geriatric domains (assessed by the GA) are associated with toxicity, QoL and physical functioning.

For cost-effectiveness, a cost-utility analysis will be performed (‘costs per quality-adjusted life year (QALY)’) from a societal perspective and with a life-long time horizon, in accordance with the Dutch guidelines for economic evaluations in healthcare.^30^ Costs will include the chemotherapy and other hospital costs (assessed from study registrations) and home and informal care (assessed using patient questionnaires at 1, 3, 6, 9 and 12 months). No impact on productivity costs will be assumed, because of the patients’ age. QALYs will be calculated using the Dutch tariff for the five-level EQ-5D questionnaires filled out by patients.^19^ Mathematical modelling will be used to extrapolate outcomes to a life-time horizon. In the analysis, incremental costs and QALYs will be compared using net-benefit analysis, according to intention to treat.^31^

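### Cumulative received dose, which accrues after randomisation and stops at progression, is listed with baseline factors as a covariate for survival

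*Protocol article*

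**What the plan says.** All references are to the protocol article.

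- *Statistics: analysis* gives the non-inferiority rule (upper confidence limit of the HR below 1.25) without naming the model that supplies the HR. The next sentence plans univariable and multivariable Cox models "to investigate the effect of age, comorbidity, the geriatric domains, cumulative received dose and tumour characteristics on survival". No time-dependent coding or landmark is mentioned.
- The sentence after that concerns the treatment effect among risk groups. It adds an interaction term (its two components are missing from the sentence; arm and risk group are implied) that "will be included in the model together with additional targeted therapy and centre".
- *Secondary outcomes*: "A logistic regression model will be estimated to study the effect of groups on chemotherapy-related toxicity", and "the same covariates as discussed before will be included".
- Dose is also an endpoint. *Outcome measures* lists "OS, cumulative received dose and cost-effectiveness in the first year", and *Secondary outcomes* states: "The cumulative dose received by patients in each arm (divided by BSA) will be reported, and means will be compared using the t-test". *Study objectives* names a higher cumulative dose as a hoped-for effect of the intervention.
- What determines dose: "In the dose-reduced arm, patients receive an upfront 25% reduction (75% of full dose" (*Doublet chemotherapy*; the monotherapy section has the same reduction), with cuts after toxicity and optional escalation after two well-tolerated cycles. On duration, *Treatment monitoring* says: "Chemotherapy treatment will be continued until progression, unacceptable toxicity or a patients’ or clinicians’ decision to stop".

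**The concern.** Total dose is known only once treatment has ended, and treatment normally ends at progression. A Cox model that starts at randomisation and takes total dose as fixed therefore uses the future to explain the present: patients who progress late have had time to receive more drug. The coefficient then favours higher dose even if dose does nothing. In a trial that asks whether less drug is good enough, this is a misleading result on the central question, even if the model is only a prognostic-factor analysis.

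If arm is in the same model, there is a second problem. Dose is a consequence of arm, so the arm estimate is no longer the randomised contrast. The interaction sentence adds its term to *the model*, and the models just described are the ones containing dose. If the toxicity model also takes dose, it conditions on something caused by both the arm and the toxicity being modelled.

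**Working it through.** **1. Plan's own figure.** The concern rests on no stated figure, but the design inputs set up the check. Schoenfeld events for margin 1.25, one-sided 5%, 80% power: 4 × (1.645 + 0.842)² / (ln 1.25)² = 497. With hazard 0.12, uniform accrual over 36 of 48 periods, the event probability is 1 − (e^(−0.12×12) − e^(−0.12×48)) / (0.12×36) = 0.946. Then 497 / 0.946 gives 526 (530 by Freedman), against the stated 528, and 528 / 0.9 = 587. The design reproduces with a one-sided 5% level, so pass rates below use a one-sided 95% limit.

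**2. Mechanism by hand.** Take three-week cycles with no toxicity and no dose effect. In the full-dose arm, progression at 24 weeks means 8 full-dose cycles and at 48 weeks 16: dose tracks PFS because it is a count of progression-free time. Now hold total dose at 6 full-dose cycles. A full-dose patient reaches it at 6 × 3 = 18 weeks. A reduced-dose patient needs 6 / 0.75 = 8 cycles, or 24 weeks. At equal total dose the reduced arm has the longer PFS by construction, which lowers the adjusted arm HR. Stopping for toxicity weakens or reverses this, because a patient who stops early can have a low dose and a long PFS, and this happens more often in the arm with more toxicity.

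**3. Simulation.** 528 patients, hazard 0.12, 200 trials per scenario, no causal effect of dose on PFS.
- From the protocol: sample size, hazard, accrual pattern, 75% starting dose, 25% cuts.
- From the phase II trial cited in the *Introduction*, as an assumption here: toxicity 62% versus 43%.
- Further assumptions: an unmeasured frailty affecting both PFS and toxicity; toxicity within about the first 4 months; 20%, 50% or 80% of patients with toxicity stopping, the rest reduced; 20% escalation among reduced-arm patients without toxicity; dosing capped at 24 months.

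| True HR | Stop after toxicity | Arm HR, dose omitted | Arm HR, total dose included | HR per full-dose cycle | Limit < 1.25, dose omitted | Limit < 1.25, dose included |
|---|---|---|---|---|---|---|
| 1.00 | 20% | 1.00 | 0.83 | 0.87 | 78.0% | 97.5% |
| 1.00 | 50% | 1.01 | 0.97 | 0.91 | 72.5% | 80.0% |
| 1.00 | 80% | 1.01 | 1.02 | 0.92 | 79.0% | 69.0% |
| 1.25 | 20% | 1.24 | 0.94 | 0.86 | 5.5% | 81.5% |
| 1.25 | 50% | 1.23 | 1.12 | 0.90 | 4.5% | 35.0% |
| 1.25 | 80% | 1.23 | 1.23 | 0.92 | 6.0% | 10.5% |

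The Monte Carlo standard error of the 35% is √(0.35 × 0.65 / 200) = 3.4 points. With an 8-month median instead (hazard ln 2 / 8 = 0.0866), true HR 1.25 and 50% stopping, the arm HR moves from 1.23 to 1.13 and the pass rate from 8% to 31%. With equal toxicity (50% in both arms), true HR 1.00 and 50% stopping, the arm HR moves from 1.00 to 0.81.

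A separately built simulation (median 8 months, other assumed toxicity and stopping rates) moved a true 1.25 to 1.15–1.17 and the pass rate from about 4% to 25%. It showed a false 14–15% hazard reduction per full-dose month.

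**4. Toxicity odds ratio for arm.** In the first simulation, at true HR 1.00, including dose moved it from 0.54 to 0.53, 0.54 to 0.50 and 0.57 to 0.51 (20%, 50%, 80% stopping), away from 1. With equal true toxicity risk it moved from 1.01 to 0.91. The second simulation moved it from 0.59 to 0.63, towards 1. The two disagree in direction.

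**The case against.** The strongest reply is that the Cox sentence is a prognostic-factor analysis. It follows the non-inferiority rule as a separate sentence, arm is not among its factors, and the sample size rests on a logrank test. Nothing says that the HR compared with 1.25 comes from it. This stands. A reader might infer that the primary test is biased towards non-inferiority; the documents do not support that. They leave the source of the HR open, so the pass rates above are conditional. Nor is the direction fixed: with 80% stopping, a true 1.00 became 1.02 and its pass rate fell.

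Second, the toxicity model's reference to covariates discussed before may mean only targeted therapy and centre, the last terms named for inclusion. That reading is tenable. The wider list is the other candidate, and the text does not decide between them.

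Third, the coding of dose could be settled in an analysis plan that is not shown. This also stands in part: the bias follows if dose enters as a fixed total, which the article does not say outright. But the article makes a positive choice by placing dose in one list with baseline factors and adding no qualification. The silence is not the point; the listing is. No reading makes a fixed total-dose covariate valid for survival counted from randomisation.

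**Conclusion.** The concern holds in graded form.

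- **Survival models.** Total dose as a fixed covariate gives a spurious benefit of higher dose. This appeared in every scenario run: HR 0.86 to 0.92 per full-dose cycle with no true effect. It does not depend on whether arm is in the model. The simulations address PFS; *survival* in the sentence is not defined further.
- **Arm and arm-by-risk-group estimates from the same model.** These would be adjusted for a consequence of arm. Across 20% to 80% stopping, a true 1.25 became 0.94 to 1.23 and a true 1.00 became 0.83 to 1.02 (0.81 with equal toxicity). Size, and in some scenarios direction, depend on the assumed stopping share.
- **Primary non-inferiority test.** Affected only if its HR is taken from this model, which the text neither says nor excludes. In that case false non-inferiority at a true HR of 1.25 was 10.5% to 81.5%, against about 5–6% without dose.
- **Toxicity model.** Affected only if dose is among its covariates. The shifts were modest and of unpredictable sign.

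The toxicity, stopping and frailty inputs are assumptions, so the ranges illustrate the problem and do not forecast this trial.

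**What to change.** Amend the analysis text, before any results by arm are seen, to state that:

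1. Every model that estimates an arm effect (the primary HR, the risk-group interaction and the toxicity model) uses baseline covariates only.
2. The HR tested against 1.25 comes from a named model that does not contain cumulative dose.
3. Total dose is removed as a fixed covariate from the univariable and multivariable survival models and is reported as an outcome by arm, as already planned.
4. Any dose-survival question is a separate exploratory analysis, either landmarked (for example, dose over the first two cycles among patients still at risk) or with dose as a time-updated exposure.
5. The covariates of the toxicity model are listed by name, replacing the back-reference.

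The cost is a few sentences. No new data are needed, and the 528 and 587 patients are unchanged.
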